### Patient and public involvement

THE HOPE comprises a novel culturally appropriate early intervention for FEP that will involve patient and public community engagement at every stage of the research (intervention development, feasibility RCT and process evaluation). Key stakeholders, including service users, care providers, cultural groups, community experts and policymakers, will be consulted at each stage of the research process. Keele patient and public involvement and engagement group and service users’ group in Peshawar, Pakistan provided key inputs in developing the study design.

### Participant eligibility criteria

We will recruit patients (aged 14–25 years) residing in one of the UCs in district Peshawar with first ever psychotic episode who have not received antipsychotic medication previously, or if they already have used antipsychotic medications, it was for no longer than 6 weeks.^28^ The FEP diagnosis will be made at an interview by psychiatrists based on the International Classification of Diseases, 11th revision (ICD-11) criteria for schizophrenia, persistent delusional disorder, acute and transient psychotic disorders, schizoaffective disorder, mood disorders (mania, severe depressive episode, bipolar affective disorder) with psychotic symptoms.

The exclusion criteria will be: (1) evidence of overt learning disability; (2) organic brain damage or pervasive developmental disorder; (3) severe substance abuse (except nicotine dependence); and (4) a young person or parent not willing to provide informed consent.

### Recruitment

Participants suspected of having FEP will be identified from the following possible sources: (1) potentially eligible participants seen by TSHs, (2) potentially eligible participants identified by the PCPs, (3) those presenting in mental health services with suspected FEP and have been in contact and receiving treatment from a TSH in the area.

The cluster allocation will determine the treatment path for each participant. It is possible, for example, that a potentially eligible patient residing in the control cluster presents to the TSH in the intervention arm and vice versa. In such a case, the patient will be given the choice of visiting the nearest TSH based in the control arm (and vice versa). Otherwise, he/she will not be included in the study.

To avoid any selection bias in both groups, the recruitment into the study (both arms) would be done using the same methods by an independent researcher who would enrol in a non-selection bias way that gives parity/equality in uptake. The baseline information about all suspected cases of psychosis by TSHs will be collected, including symptomatology and demographic features. Those with a confirmed diagnosis of psychosis (by the psychiatric team following the procedures given below) will be treated in one of the treatment arms.

Potential participants will be verbally informed about the trial by the TSHs, PCPs or research assistant (RA) working with the research team. Patients who agree to participate will be given a full written information sheet about the study by an RA (written information sheets read by RA for those who cannot read) about the study. In case of a young person below the age of 16 years, written informed consent will be obtained from the patient and the parent, who will almost always be accompanying the young person (online supplemental appendices 1 and 2). For illiterate participants, witnessed oral consent and a thumbprint in lieu of a signature will be sufficient. The witness will not be a member of the research team. Both alternatives to full written consent are routinely practised in Pakistan, are culturally acceptable and have been used in our previous studies in this setting^27 29^ (see figure 2).

10.1136/bmjopen-2023-072471.supp1Supplementary data

Those willing to participate will be requested to complete the baseline sociodemographic data and a suicide risk screen based on the MhGAP intervention guide by an RA. In case of any concerns about the safety of the individual due to suicide risk, the RA will seek help from psychiatric services following the study standard operating procedure developed for this purpose.

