### Randomisation

Randomisation will occur at the UC level and be allocated using a 1:1 ratio to either the intervention arm (THE HOPE) or enhanced treatment as usual (ETAU) and stratified by urban/rural setting.

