##### Outcome measures

###### Primary outcome measures

Key feasibility outcomes for the trial will include the total number of cases recruited in the 12-month period and cases referred by TSHs and PCPs to psychiatrists with suspected FEP during the recruitment period. It will also include the number of FEP cases suspected by TSHs and PCPs and the likelihood of the confirmed diagnosis of FEP based on interview diagnosis by psychiatrists and DUP in those meeting criteria for FEP.

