##### Blinding and allocation concealment

It is not possible to blind study participants from their treatment arm allocation. However, the assessment team conducting the baseline and follow-up assessments will be blinded to the treatment arm of the cluster. During all assessments, the key feasibility outcome measures will be completed first to minimise the risk of bias in the event of unblinding, and if it occurs, the point of unblinding will be recorded. Sensitivity analyses will be carried out to assess the effect of unblinding on the clinical outcomes. The trial statistician will be blind to allocation status. The psychiatrist diagnosing FEP will be blind to the diagnosis given by PCPs and the impression of illness by TSHs. This will help to minimise the bias and provide a good measure of training intervention.

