### Data analysis

#### Quantitative analysis

Being a feasibility trial, the main analysis will focus on process outcomes and include estimation (with one-sided and two-sided 80% and 90% CI estimation) of the number/proportion of potentially eligible patients, consent rate, overall uptake rate (in relation to number potentially eligible), average cluster sizes (and variation in cluster sizes) and treatment fidelity—the proportion of patients having the protocolled intervention pathway (intervention arm), intervention acceptability, assessment of possible contamination effect across clusters, overall retention/follow-up rate of participants. Our point and interval estimates will be considered alongside target success criteria for informing overall feasibility and potential progress to a main RCT.

We will also calculate means and CIs of clinical outcomes (both within-study and between-study groups) and determine which outcome(s) is/are most sensitive to change, and evaluate parameters required in order to inform the sample size calculation for the main trial.

Due to the lack of similar studies in this area, it is not possible to suggest clear progression criteria to guide the decisions about the feasibility of proceeding to a definitive trial in future. We suggest following a priori progression criteria in order to guide the feasibility of a future definitive trial. In light of the following criteria, the trial findings will be presented to the steering committee, which will advise about the feasibility of proceeding to the definitive trial.

**Red**, that is, the progression to a definitive trial using the proposed intervention and procedures is not feasible. Recruitment below 90 in total (45 in both arms) over a 12-month period, less than 70% of recruited sample completed all follow-up visits, and less than 70% of TSHs in both arms consented, participated in the training and worked with psychiatric services in referring the suspected cases.

**Amber**, that is, the progression to a definitive trial using the proposed intervention is feasible but would require modifications in the intervention, recruitment or follow-up procedures. Recruitment of 90–130 participants in total over a 12-month period, 70%–80% of recruited sample completed all follow-up visits, and 70%–85% of TSHs in both arms consented, participated in training and worked with psychiatric services in referring the suspected cases.

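### Equal uptake in the two arms is written as a goal of enrolment, although each patient's arm can be known beforehand and uptake and recruitment are quantities the trial estimates

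*Protocol article*

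**What the plan says.** The Recruitment section gives the safeguard in one sentence. It opens: "To avoid any selection bias in both groups, the recruitment into the study (both arms) would be done using the same methods". It then assigns the work to an "independent researcher who would enrol in a non-selection bias way that gives parity/equality in uptake".

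Four other parts of the article bear on it:

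- **Allocation.** Under Randomisation: "Randomisation will occur at the UC level and be allocated using a 1:1 ratio to either the intervention arm". Under Recruitment: "The cluster allocation will determine the treatment path for each participant".
- **Patients who present across arms.** A patient living in a cluster of one arm may go to a healer (TSH) of the other. The article says: "In such a case, the patient will be given the choice of visiting the nearest TSH based in the control arm (and vice versa". Otherwise the patient is not included.
- **Blinding.** Under Blinding and allocation concealment, "the assessment team conducting the baseline and follow-up assessments will be blinded to the treatment arm of the cluster". The statistician is also blind, and the diagnosing psychiatrist is blind to the primary care and healer impressions. The enroller is not mentioned.
- **Outcomes.** Under Primary outcome measures: "Key feasibility outcomes for the trial will include the total number of cases recruited in the 12-month period". The Quantitative analysis section estimates "consent rate, overall uptake rate (in relation to number potentially eligible), average cluster sizes (and variation in cluster sizes". Total recruitment is one of the three items in the Red, Amber and Green criteria, with cut-points at 90 and 130.

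**The concern.** Using the same methods in both arms is a procedure. Equal uptake is a result. The sentence asks for both, and the second does not serve its stated aim: two arms can have the same uptake and still differ in who was enrolled.

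If the enroller tries to produce equality, he or she must know how the arms are running and which arm the next patient belongs to, and must vary effort or selectivity accordingly. Enrolment then depends on a known allocation, which is the usual route to selection bias in a cluster trial that recruits after randomisation.

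Unequal recruitment is also plausible by design. Only the intervention arm's primary care physicians receive the extra early-detection training, and only its healers are trained specifically to identify and refer first-episode psychosis. At stake are the recruitment rate, uptake and cluster-size variation carried into the definitive trial, the comparability of the enrolled patients behind the between-group clinical means, and possibly the recruitment item of the progression decision.

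**Working it through.** **1. Can the enroller know the arm?** The arm follows from the union council. The cross-arm rule can be applied only if someone in recruitment knows the arm of the patient's residence and of the healer. Study procedures has the research assistant refer suspected cases to psychiatrists assigned to each arm. No masking of the enroller is stated. Knowledge of the arm is therefore a strong inference, though not an explicit statement.

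**2. Does the plan's own precision figure depend on the clause?** Sample size gives margins of 0.1 (one arm, n = 45) and 0.07 (overall, n = 90) for a one-sided 90% bound. With z = 1.2816 and p = 0.5, and no design effect:

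- n = 45: 1.2816 × √(0.25/45) = 0.0955
- n = 90: 1.2816 × √(0.25/90) = 0.0675

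Both reproduce, and neither depends on the clause. The issue is bias in what is estimated, not its stated precision.

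**3. What would the clause do?** The article gives no expected uptake or yield by arm, so the inputs below are assumptions shown as ranges.

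*Reading A, identical procedure in both arms.* Nothing changes.

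*Reading B, equal proportions.* This is closest to the article, which defines uptake relative to the number potentially eligible. Assume 100 eligible per arm. Total = 100 × (control uptake + intervention uptake). Parity sets both to the lower or both to the higher value.

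| True uptake, control / intervention | No parity goal: total (overall uptake) | Higher arm held back | Lower arm pushed up |
|---|---|---|---|
| 0.45 / 0.55 | 100 (0.50) | 90 (0.45) | 110 (0.55) |
| 0.45 / 0.65 | 110 (0.55) | 90 (0.45) | 130 (0.65) |
| 0.45 / 0.75 | 120 (0.60) | 90 (0.45) | 150 (0.75) |

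The true arm differences of 0.10, 0.20 and 0.30 become 0 under either route. The total falls under one route and rises under the other. With no parity goal, all three totals are Amber (90–130). Holding back gives 90, the floor of Amber. Pushing up gives Amber, Amber and, at 150, Green. In the last row, average cluster size over 93 union councils is 120/93 = 1.29, against 90/93 = 0.97 or 150/93 = 1.61.

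*Reading C, equal counts.* Assume 65 eligible in control, uptake 0.70 in both arms, and the larger arm held back.

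- Intervention eligible 100: free total 45.5 + 70 = 115.5. Equal counts give 91, and apparent intervention uptake is 45.5/100 = 0.455. Both totals are Amber.
- Intervention eligible 130: free total 45.5 + 91 = 136.5 (Green). Equal counts give 91 (Amber), and apparent uptake is 45.5/130 = 0.35.

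Alternatively, fix control at the planned 45 and let the intervention arm yield r times as many consenting eligible patients. The number unenrolled is 45r − 45: about 11, 23 and 45 for r = 1.25, 1.5 and 2. Free totals are about 101, 113 and 135, against 90. Only r = 2 crosses 130.

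Reading C is weaker than B. In its examples uptake as a proportion is already equal at 0.70, so parity in the article's own sense would require no loss at all.

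**4. What stays visible?** Suspected and referred cases and confirmed diagnoses are separate primary outcomes that arise before enrolment. Baseline information is collected on all cases suspected by healers. Table 1 places duration of untreated psychosis at screening. Arm differences in these would still be seen.

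**The case against.** Read whole, the sentence may mean only equal opportunity through identical procedures. No quota, cap, matching rule or stopping of the busier arm appears anywhere. Ninety is a minimum and Green needs more than 130, which argues against any cap. The named outcomes are a total and an overall rate, not arm contrasts. The trial plans no hypothesis test, and a steering committee advises on progression. The article is condensed, and operating procedures that are not shown may describe how patients are approached.

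Most of this limits the size of the point. A reader might infer that every true arm difference will be suppressed and the recruitment total lowered. The documents do not support that: no mechanism is stated, parity could be sought through more effort in the lagging arm, and the pre-enrolment counts remain visible.

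It does not remove the point. Identical methods are already required earlier in the sentence, so the parity clause is either redundant or an aim for enrolment. Outcomes stated as totals are not protected, since varying effort by arm moves the total, overall uptake and cluster sizes as well. Nor does the point rest on missing detail: it concerns a goal the article states.

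**Conclusion.** The point holds as a fault in a stated recruitment goal, worth correcting at medium confidence. Equal uptake should be observed, not produced, and it is no guard against selection bias. If the clause is followed literally by an enroller who knows the arm, it could distort the recruitment and uptake estimates, cluster sizes, the mix of enrolled patients and possibly the recruitment item of the progression criteria.

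No single magnitude can be given. Under the assumed inputs the effect runs from nothing (identical procedure) to a shift of one progression band in either direction: 136.5 to 91 with equal counts, or 120 to 150 with equal proportions reached by extra effort. Only the more extreme assumed values cross a threshold. It would go too far to say that the trial will enrol unequally by design or that its case-finding signal is lost. Any effect on duration of untreated psychosis is confined to the enrolled sample.

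**What to change.** Delete the closing clause on parity in uptake. State instead that the independent researcher approaches every consecutive potentially eligible patient in both arms, uses the same eligibility and consent procedures, and has no arm-level target or cap. Add that numbers suspected, eligible, approached and enrolled, and uptake, are reported by arm as observed.

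Masking of the enroller should be asked for only where it is compatible with the cross-arm redirect rule and the arm-assigned psychiatrists, for example if someone else handles redirects. The essential change does not depend on it.

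The cost is about one sentence in the protocol and the recruitment procedure. The independent researcher is already planned and suspected cases are already recorded. The small downside is that arm sizes may be unequal. If only identical procedure was meant, nothing is lost.

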### Study procedures and data collection

The RA will refer all suspected cases from TSHs and PCPs to the psychiatrists assigned to each arm, who will independently assess patients within 48 hours of referral, being blind to the diagnosis (by PCPs) or impression of TSHs. The ‘diagnosis’ of FEP by TSHs will be recorded using an instrument developed in consultation with TSHs. This instrument will indicate the likelihood of a person suffering from FEP, as judged by the TSH. Separately, TSHs will also be asked to identify the lay terminology they use in their routine work to capture their conceptualisation of FEP. For patients referred from primary care, PCPs will be asked to provide the likely diagnosis based on ICD-10 (see figure 2).^30^

**Figure 2 F2:**
[figure not shown]
Patient flow and assessments in THE HOPE trial. FEP, first-episode psychosis; PCPs, primary care physicians; PIS, participants’ information sheet; THE HOPE, Traditional HEalers working with primary care and mental Health for early interventiOn in Psychosis in young pErsons; TSH, traditional and spiritual healer.

The psychiatrists will be trained to achieve adequate inter-rater reliability in making the FEP diagnosis. The psychiatrists will diagnose based on the ICD-10 criteria of FEP described above.

Those diagnosed with FEP will be started on treatment in collaboration with participating PCPs or TSHs (if the patients and family want to continue treatment by TSHs) in the intervention arm, while those in the control arm will be provided with the treatment as usual. The treatment will be based on recent guidelines for the treatment of FEP adopted for the purpose of the study.

#### Quantitative data collection and follow-up

Once the participant has provided informed consent, trained RAs will collect the demographic information and complete baseline assessment and suicide risk screen based on the MhGAP intervention guide. Follow-up data will be collected 12 weeks post-baseline by the RAs blinded to the allocation status.

##### Outcome measures

###### Primary outcome measures

Key feasibility outcomes for the trial will include the total number of cases recruited in the 12-month period and cases referred by TSHs and PCPs to psychiatrists with suspected FEP during the recruitment period. It will also include the number of FEP cases suspected by TSHs and PCPs and the likelihood of the confirmed diagnosis of FEP based on interview diagnosis by psychiatrists and DUP in those meeting criteria for FEP.

###### Secondary outcome measures

In addition to feasibility outcomes, the study will aim to measure a range of clinical outcomes and service utilisation measures for assessing the feasibility and acceptability of the intervention. In addition, process evaluation (see below) will be done using qualitative methods. Table 1 provides details of these outcomes and the baseline and follow-up points for these assessments.

**Table 1 T1:** Data collection schedule and list of assessments

Description	Measure	Screening assessment	Baseline assessment	4 weeks post-baseline	3 months post-baseline
Age	Date of birth	✓			
Gender	Male/female	✓			
Education	Years spent in education	✓			
Marital status		✓			
Work status		✓			
Psychopathology	Brief Psychiatric Rating Scale^31^		✓		✓
	Young Mania Rating Scale^32^		✓		✓
	Hamilton Depression Rating Scales^33^		✓		✓
	Clinical Global Impression Scale^34^		✓		✓
Occupational and social functioning	Global Assessment of Functioning^35^		✓		✓
Duration of untreated psychosis	Comprehensive Assessment of At-Risk Mental States^36^	✓			
Quality of life	EuroQol-5^37^		✓		✓
Family burden	Perceived Family Burden Scale^38^		✓		✓
Perceived stigma	Internalised Stigma of Mental Illness^39^		✓		✓
Physical health	Weight and body mass index		✓		✓
Substance abuse	Drug Abuse Screening Tool^40^		✓		✓
Response to antipsychotic treatment	Brief Psychiatric Rating Scale^31^			✓	
Adherence to antipsychotic treatment	Medication Adherence Rating Scale^41^				✓
Rates of disengagement	Response to contact requests for a consecutive 4-week period during follow-up				✓
Remission rates	Score of 3 or below on the Brief Psychiatric Rating Scale,^31^ maintained at least for 3 months		✓		✓
Service utilisation metrics	indicated by: Number of TSHs approached, consented and completed the training programme Patients screened for suspected psychosis Total number of confirmed cases	✓	✓		✓
The acceptability of trial procedures	Adherence to trial procedures and completion of the assessments at baseline and 12 weeks		✓		✓
Fidelity of intervention	First-Episode Psychosis Services Fidelity Scale, modified and adapted for the local settings^43^		✓		✓
Implementation costs	The Client Service Receipt Inventory^44^		✓		✓

TSHs, traditional and spiritual healers.

**Psychopathology:** Brief Psychiatric Rating Scale (BPRS),^31^ Young Mania Rating Scale,^32^ Hamilton Depression Rating Scale,^33^ and Clinical Global Impression Scale^34^ for measuring improvement in symptoms and remission rates.**Functioning:** Global Assessment of Functioning.^35^**DUP:** Comprehensive Assessment of At-Risk Mental States at baseline.^36^**Quality of life:** EuroQol-5.^37^**Family burden**: Family Burden Scale.^38^**Stigma**: Internalised Stigma of Mental Illness.^39^**Physical health**: weight and body mass index.**Substance abuse**: Drug Abuse Screening Tool.^40^**Response to antipsychotic treatment:** change in BPRS^31^ from baseline to 4 weeks after starting antipsychotics.**Adherence to antipsychotic treatment:** Medication Adherence Rating Scale.^41^**Rates of disengagement** are defined as a participant’s refusal to engage with treatment or not responding to contact requests for a consecutive 4-week period during follow-up while still residing within the study site catchment area.^42^**Remission rates:** improvement in psychotic symptoms from baseline (operationalised as a score of 3 or below on the BPRS^31^), maintained for 3 months.**Service utilisation metrics** measures will be used as a measure of the acceptability of the intervention. These will include patients screened for suspected psychosis out of all those presenting to at different contact points, the median time taken in screening, frequency and duration of contacts, the median length of time to treatment from assessment to starting treatment, the proportion of cases identified as at-risk mental state for FEP out of total accepted cases and the willingness of TSHs to work with health services (indicated by the number of TSHs approached, consented and completing training programme).**The acceptability of trial procedures** will also be assessed through adherence to trial procedures and completion of the assessments at baseline and 12 weeks.**Fidelity of intervention:** FEP Services Fidelity Scale, modified and adapted for the local settings,^43^ will be used to assess the degree to which mental health teams deliver evidence-based care for FEP.**Implementation costs:** the Client Service Receipt Inventory^44^ will measure direct and indirect costs in implementing the intervention to estimate health economic costs from the payer and provider perspective. We will estimate mean, median and quartile costs at each time point.

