### Study timeline

We aim for the pilot RCT to start on 1 April 2023. Recruitment will commence when the trial commences and will be conducted until 1 April 2024; there will be a 3-month follow-up after the recruitment of the last patient. We anticipate that the analysis will start in September 2024.

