### End of trial

The end of the study is defined as when the 12-week follow-up assessment and all qualitative interviews have been completed. Keele University ethics and the ethics board in the local context will be notified of the end of the study.

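### Remission must be held for 3 months, but follow-up ends 12 weeks after baseline, so the outcome cannot be assessed as worded

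*Protocol article*

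**What the plan says.** **Definition.** In the Protocol article, Secondary outcome measures, the remission row of Table 1 asks for a BPRS score of 3 or below, "maintained at least for 3 months". The list of measures below the table describes remission as "improvement in psychotic symptoms from baseline", with the same threshold, "maintained for 3 months".

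**Schedule.** In Table 1 the BPRS is ticked at baseline and 3 months under psychopathology, and at 4 weeks under response to antipsychotic treatment. The remission row is ticked only at baseline and 3 months. Table 1 counts the 4-week rating from baseline, whereas the text describes the change "from baseline to 4 weeks after starting antipsychotics".

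**End of observation.**
- Quantitative data collection and follow-up: "Follow-up data will be collected 12 weeks post-baseline by the RAs blinded to the allocation status".
- Study timeline: "there will be a 3-month follow-up after the recruitment of the last patient".
- End of trial: "The end of the study is defined as when the 12-week follow-up assessment and all qualitative interviews have been completed".

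No later clinical visit and no retrospective rating is described.

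**The concern.** The definition contains a minimum duration as long as the whole follow-up, and the clock can start only after baseline because the state has to be an improvement on baseline. The two conditions cannot both be satisfied inside the observation period. This is a conflict between two things the article states, not a detail left to a fuller document. An analysis plan cannot create ratings after week 12. It could only change the definition.

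What is at stake is the pilot's benchmarking role. The Objectives include estimating parameters of candidate outcomes for a future sample size, and Quantitative analysis says the team will find which outcomes respond most to change. A remission rate computed to the letter would look unresponsive for a reason unrelated to treatment. If the duration clause were dropped silently at analysis, the reported rate would not match its published definition, and that choice would be made after the data had been seen.

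**Working it through.** There is no plan figure to reproduce. The check is arithmetic on the visit schedule.

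**Inputs**
- BPRS times: 0, about 4 and 12 weeks (Table 1).
- Last clinical assessment: 12 weeks after baseline (Quantitative data collection and follow-up; End of trial).
- Required maintenance: 3 months. The article uses 12 weeks and 3 months for the same visit, so I take 12 weeks.
- Start of the remitted state: after baseline (improvement clause).

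**General condition.** If the threshold is first met at time *t*, the observable maintenance is 12 − *t* weeks. The definition needs 12 − *t* ≥ 12, that is *t* ≤ 0. The improvement clause needs *t* > 0. No *t* satisfies both.

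**At the scheduled ratings**

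| Threshold first met | Observable maintenance | Shortfall against 12 weeks | Follow-up needed to see 12 weeks |
|---|---|---|---|
| 4-week rating | 12 − 4 = 8 weeks | 4 weeks | 4 + 12 = 16 weeks |
| 12-week visit | 12 − 12 = 0 weeks | 12 weeks | 12 + 12 = 24 weeks |

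Taken alone, the remission row has a single post-baseline tick (3 months), so it supplies no observed maintenance at all. The 8-week window exists only if the 4-week rating is borrowed from the treatment-response row.

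**Sensitivity to calendar months.** Three calendar months are about 13 weeks. If the last visit is also at 13 weeks, the window from week 4 is 13 − 4 = 9 weeks against 13, again 4 weeks short. Mixing the two conventions gives a shortfall of 13 − 8 = 5 weeks or 12 − 9 = 3 weeks. The conclusion does not change.

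**Sensitivity to the 4-week anchor.** Suppose the rating is counted from the start of antipsychotics.
- If treatment starts *d* weeks after baseline, the rating falls at 4 + *d* weeks and the window is 8 − *d* weeks.
- If treatment started *p* weeks before baseline, with *p* below 4, the rating falls at 4 − *p* weeks and the window is 8 + *p* weeks, still below 12.

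So the 8-week figure depends on the anchor, but the failure to reach 12 weeks does not.

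**Edge case.** Participant eligibility criteria admits patients with earlier antipsychotic use provided "it was for no longer than 6 weeks". Such a patient might already score 3 or below at baseline and again at 12 weeks, and would then fit the bare wording of Table 1. The improvement clause in the list of measures excludes that patient.

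**The case against.** **The authors may have meant remission present at the end of the 3-month follow-up.** The ticks at baseline and 3 months make a drafting slip plausible. But the Table 1 wording sets a minimum duration, not a time point. If a time point was intended, the sentence still needs correcting. This argument explains the error and does not remove it.

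**The outcome carries little weight.** This stands. Remission is one of many secondary measures. It is not among the primary feasibility outcomes, and it appears in none of the red, amber or green criteria, which use recruitment, completion of follow-up and healer participation. The article proposes no formal hypothesis testing.

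**The data are not lost.** This also stands. A reader might infer that the pilot can yield no usable remission proportion. The documents do not support that: the 12-week BPRS score is collected, and a point proportion can be taken from it. What fails is the match between the stated definition and the data.

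**A rate of exactly zero is too firm.** A reader might infer 0 of the planned 90 participants, or 0% in both arms, by construction. That follows only when the improvement clause is applied. Table 1 alone leaves the edge case of a partly treated patient with a low baseline score. Not assessable as worded is the accurate description.

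**Conclusion.** The point holds. Remission as defined cannot be demonstrated within the planned follow-up. With the 4-week rating taken at 4 weeks after baseline, the longest observable maintenance after a post-baseline remission is about 8 weeks against 12 required, a shortfall of 4 weeks. Read literally with the improvement clause, no participant can qualify.

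This rests on three assumptions: the article's own equation of 3 months with 12 weeks, no BPRS rating beyond those in Table 1, and improvement from baseline being part of the definition.

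The wording is wrong and should be fixed, but it is not critical. The progression decision is unaffected, and the other clinical scales still serve the benchmarking aim.

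**What to change.** In the list of secondary measures and in Table 1:

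1. Replace the 3-month maintenance clause with *BPRS criterion met at the 12-week visit*.
2. Keep the baseline rating, and its tick in the remission row, as the reference for improvement.
3. Optionally add a sustained version, *criterion met at both the 4-week and 12-week ratings*, with a 4-week tick in the remission row. Before doing so, reconcile whether that rating is counted from baseline (Table 1) or from the start of antipsychotics (text), because the length of the sustained period depends on it.
4. State that 3-month sustained remission cannot be assessed in this study.

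This is a change of wording that uses ratings already planned, with no new visit or participant burden. The downside is that the outcome becomes a point remission, or one of roughly 8 weeks. Keeping the 3-month clause would instead require BPRS ratings to at least 16 weeks after baseline for those first meeting the threshold at week 4, and to 24 weeks for those first meeting it at the present last visit.
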